#### Evaluation of clinical effectiveness

Clinical effectiveness of the intervention will be evaluated based on analysis of impact on key clinical outcome measures. The primary outcome for evaluation of clinical effectiveness is change in proportion of the target population prescribed secondary prophylaxis for RHD by the end of the study compared with a baseline timepoint prior to the date of echocardiographic active case finding (table 3).

**Table 3 T3:** Clinical effectiveness evaluation outcome measures

Outcome measure	Data collection	Data variables	Data analysis

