The primary outcome will be reported for all communities as well as aggregated results for Australia and Timor-Leste. This primary outcome represents a clinically meaningful outcome demonstrating whether active case finding for RHD results in a change in practice at the individual patient level that has a measurable public health impact in terms of increased access to guideline-based care. The proportion of the population prescribed secondary prophylaxis is expected to increase with detection of new RHD cases but may also be reduced as people complete treatment. The number of people in each community who are commenced on secondary prophylaxis and the number of people in each community who cease secondary prophylaxis during the study period will be collected as secondary outcomes. Other secondary outcomes include elements of the cascade of care from diagnosis to antibiotic adherence (online supplemental material (Cascade of Care).

This study will also report on maternal and birth outcomes in women found to have RHD on echocardiographic screening, and prevalence of RHD in screened populations (table 3).

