#### Sample size calculation

The sample size has been calculated based on the primary outcome measure. To observe an absolute increase of 2.4% of the target population prescribed secondary prophylaxis, from a baseline prevalence of 4.4% to 6.8% (based on previous data from the Northern Territory^3^), with 95% two-sided significance and 80% power, the sample size required is 1421. However, if a lower proportion of the target population is prescribed secondary prophylaxis at baseline (as expected in Western Australia and Timor-Leste), then the power of the study is increased. The study will aim to enrol >1500 participants (children and pregnant women) across approximately 10 sites (~150 participants per site); five sites in Australia and five sites in Timor-Leste over 18 months.

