#### Quantitative data analysis

Quantitative analysis of clinical effectiveness data will be conducted using STATA V.18 (StataCorp, USA). The proportion of the target population prescribed secondary prophylaxis will be calculated prior to recruitment and screening participants, and at completion of the study, and will be described with 95% CIs. Numerator data will be obtained from clinic and RHD register data; the denominator will be based on census population data or health information system population data, following consultation with the community-led implementation group regarding the most accurate source for local population estimates.

The absolute change in proportion of the target population prescribed prophylaxis will be calculated with adjustment for clustering by community and described with 95% CIs. Proportions from commencement and completion of the study will be compared using a two-tailed comparison of proportions test. A p value <0.05 will be considered significant.

Descriptive analyses will be used to quantify secondary outcomes on the epidemiology of RHD in the target population at completion of the study. The proportion of enrolled participants progressing through each stage of the RHD cascade of care will be calculated (with 95% CI). Prevalence of RHD (and 95% CI) will be calculated for the different participating communities and jurisdictions, stratified by sex and age group, based on proportion of people screened who have a diagnosis of RHD. Prevalence of known RHD will also be estimated by calculating the proportion of people in the community with a diagnosis of RHD entered on the relevant register at completion of the study.

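### The stated 80% power belongs to an unclustered two-sample comparison of 1421 people, not to the cluster-adjusted, population-based before-after change that is the primary analysis

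*Protocol article*

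**What the plan says.** The primary clinical effectiveness outcome (Evaluation of clinical effectiveness) is the "change in proportion of the target population prescribed secondary prophylaxis for RHD by the end of the study compared with a baseline timepoint".

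The Sample size calculation section ties its figure to that outcome. It takes "To observe an absolute increase of 2.4% of the target population prescribed secondary prophylaxis", "from a baseline prevalence of 4.4% to 6.8"%, and concludes "with 95% two-sided significance and 80% power, the sample size required is 1421". Enrolment follows: "The study will aim to enrol >1500 participants (children and pregnant women"), "across approximately 10 sites (~150 participants per site"). The section adds that power rises if the baseline is lower, as it expects in Western Australia and Timor-Leste. It gives no ICC, design effect or correlation between the two time points.

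The Quantitative data analysis section says three things about the same outcome:
- The denominator comes from census or health-information-system population data for the community, not from the people enrolled.
- The absolute change "will be calculated with adjustment for clustering by community and described with 95% CIs".
- The start and end proportions are compared with a two-tailed test of proportions at p<0.05. This sentence does not repeat the clustering adjustment.

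**The concern.** The article states a power and it states an analysis, and the two do not match. The power calculation treats people as independent. The analysis treats them as grouped in about 10 communities, and it counts a different set of people.

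In a before-after design on the same communities, differences in starting level largely cancel. What costs precision is variation between communities in the change itself. The protocol gives reason to expect such variation: Table 1 lets each site tailor who screens, when, where and with which implementation strategies, and the implementation evaluation is meant to explain why success differs between sites.

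The primary claim rests on p<0.05. A non-significant result would be read against 80% power that has not been shown for the analysis producing it. If the p value ignores clustering while the confidence interval beside it does not, the two could also disagree.

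**Working it through.** **Inputs from the Sample size calculation section.** p1 = 0.044, p2 = 0.068, difference d = 0.024; two-sided alpha 0.05 (z = 1.960); power 0.80 (z = 0.842); stated size 1421; enrolment about 10 × 150 = 1500.

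**Step 1. Reproduce 1421.** Let V = p1(1−p1) + p2(1−p2) = 0.042064 + 0.063376 = 0.10544, and let p̄ = 0.056, so 2p̄(1−p̄) = 0.105728.
- Pooled: n = [1.960√0.105728 + 0.842√0.10544]² / 0.024² = 1,440 per time point.
- Unpooled: n = (1.960 + 0.842)² × 0.10544 / 0.024² = 1,437.
- Arcsine: h = 2·arcsin√0.068 − 2·arcsin√0.044 = 0.1050; n = 2(1.960 + 0.842)²/h² = 1,425.

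All three lie within about 1.3% of 1421. Other readings do not fit: continuity-corrected 1,522, one-sided 1,134, one-sample against a fixed 4.4% 654. If 1421 were the total over both time points (about 710 each), power would be only 50%. So 1421 is the size per time point for independent samples, with no design effect.

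**Step 2. Margin in the enrolment target.** Power = Φ(d/√(V/n) − 1.960).
- n = 1421: SE = 0.00861, power 79.6%.
- n = 1500: SE = 0.00838, power 81.7%.

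1500/1421 = 1.056, so the target absorbs a variance inflation of about 1.06.

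**Step 3. Illustrate the cost of clustering.** The documents give no ICC (ρ) or between-period correlation of a community's level (r), so the values here are assumptions. For m people per community at each time point, with different people at the two times, the variance of the change is inflated by 1 − ρ + mρ(1 − r). With m = 150, ρ = 0.01, 10 communities and the normal reference:

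| r | Inflation | Effective n (1500 / inflation) | Power |
|---|---|---|---|
| 0.8 | 0.99 + 0.30 = 1.29 | 1,163 | 71% |
| 0.5 | 0.99 + 0.75 = 1.74 | 862 | 58% |
| 0 | 0.99 + 1.50 = 2.49 | 602 | 44% |
| 1.0 | 0.99 | 1,515 | 82% |

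With about 10 clusters, a t reference on 9 df (critical value 2.262) would lower the first three to about 61%, 49% and 37%. The article names no reference distribution, so that too is an assumption.

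**Step 4. Forces in the other direction.** Each case changes one thing, starting from ρ = 0.01, r = 0.8 and the 71% above.
- Larger denominators: at 300 per community, inflation is 0.99 + 0.60 = 1.59, effective n = 3000/1.59 = 1,887, and power is 89%.
- The same people counted twice: with an individual-level correlation of 0.5, inflation is 0.30 + 0.99 × 0.5 = 0.795 and power is 89%.
- Lower baseline: for 2.0% to 4.4% with inflation 1.29, power is 91%.

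The community sizes, the overlap and the 2% baseline are also assumptions.

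**The case against.** The strongest reply is that none of this shows power to be below 80%. The 150 per site are enrolled participants, whereas the primary denominator is the community's target population, which may be larger. Many residents aged 5–20 would be counted at both dates. The Sample size calculation section itself expects lower baselines in Western Australia and Timor-Leste. Each of these raises power, and every ICC and correlation above is assumed. This stands. It rules out saying that the study is underpowered, or naming one corrected sample size. It does not rescue the 80%, because the article did not base that figure on community denominators, overlap or between-community variation.

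A second reply is that the test sentence describes a plain comparison of proportions, which is what 1421 was sized for. That is a fair reading, and the text does not settle it. On that reading, however, the p value and the cluster-adjusted interval beside it would rest on different variances, so the section still needs reconciling.

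A reader might also infer that the country-level results are underpowered, since the article says: "The primary outcome will be reported for all communities as well as aggregated results for Australia and Timor-Leste". The documents do not support this as a fault. They promise reporting at those levels, not a powered test, and applying the Northern Territory baseline to Timor-Leste would ignore the lower baseline expected there.

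**Conclusion.** The point holds as a mismatch between the power calculation and the analysis. The arithmetic behind 1421 is sound for two independent samples, to within about 1%. It is wrong as a description of a change that is adjusted for clustering in about 10 communities and computed on population denominators.

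The size of the error, and even its direction, cannot be fixed from the documents. Under the assumptions shown, power runs from about 44% (ICC 0.01, no between-period correlation, 150 unpaired people per community) to about 90% (larger denominators, overlap or a lower baseline). The tempting stronger statement, that the planned analysis falls short of 80%, is not established. What is established is that 80% has not been shown for it, and that the enrolment margin covers an inflation of only about 1.06 on the calculation's own terms.

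**What to change.** 1. In the Sample size calculation section, say that 1421 is the size per time point for independent samples. Then give power, or the minimum detectable change, as a range for the cluster-adjusted within-community before-after change. State the expected community denominators, the assumed between-community variation in the change (an SD of change, or an ICC with its between-period correlation), the assumed overlap of individuals, the baselines used, and a reference distribution suited to about 10 clusters.
2. In the Quantitative data analysis section, state that the p value uses the same cluster-adjusted variance as the 95% CI.

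The cost is a recalculation and a few sentences, with the single 80% replaced by a range. Enrolment and data collection do not change.

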#### Clinical effectiveness data collection

Study data will be collected using a REDCap V.13 (Vanderbilt University, USA) database,^56 57^ hosted at Menzies School of Health Research (Darwin, Australia). Data relating to the expert reviewer interpretation of SPLASH images will be entered into REDCap. Expert reviewers will also enter a brief, structured report into Tricefy that can be seen by the healthcare workers and used as part of the continued education and supervision process. The formal diagnostic echocardiogram will be performed by local service providers and images will be stored on their equipment or server based on their own policies and procedures.

Demographic and clinical data will be obtained from primary healthcare and RHD register data systems by research staff, who will enter data into REDCap. Secondary data will include: participant demographics, obstetric history (for pregnant women), history of known ARF/RHD, clinical management decisions including referrals for formal echocardiography and commencement of secondary prophylaxis, time taken for SPLASH echocardiography to be performed, formal echocardiography findings and progression through the RHD cascade of care.

#### Quantitative data analysis

Quantitative analysis of clinical effectiveness data will be conducted using STATA V.18 (StataCorp, USA). The proportion of the target population prescribed secondary prophylaxis will be calculated prior to recruitment and screening participants, and at completion of the study, and will be described with 95% CIs. Numerator data will be obtained from clinic and RHD register data; the denominator will be based on census population data or health information system population data, following consultation with the community-led implementation group regarding the most accurate source for local population estimates.

The absolute change in proportion of the target population prescribed prophylaxis will be calculated with adjustment for clustering by community and described with 95% CIs. Proportions from commencement and completion of the study will be compared using a two-tailed comparison of proportions test. A p value <0.05 will be considered significant.

Descriptive analyses will be used to quantify secondary outcomes on the epidemiology of RHD in the target population at completion of the study. The proportion of enrolled participants progressing through each stage of the RHD cascade of care will be calculated (with 95% CI). Prevalence of RHD (and 95% CI) will be calculated for the different participating communities and jurisdictions, stratified by sex and age group, based on proportion of people screened who have a diagnosis of RHD. Prevalence of known RHD will also be estimated by calculating the proportion of people in the community with a diagnosis of RHD entered on the relevant register at completion of the study.

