Additional mechanisms for push notification of SPLASH results will be developed with individual sites. These may include integration with existing electronic medical record systems, automated emails or use of secure phone messaging services such as WhatsApp or Signal. In addition, healthcare workers will be able to contact an on-call remote expert for discussion of SPLASH findings and advice regarding next steps. Non-experts will receive ongoing supervision and feedback from reviewing experts on image acquisition quality and image findings, and uninterpretable images will be reattempted. Participants with abnormal or repeated uninterpretable images should be referred by the local healthcare service for a full diagnostic echocardiogram.

Treatment decisions will usually be made following a full diagnostic echocardiogram and specialist review. If, however, the SPLASH findings are strongly suggestive of RHD, or there are other clinical indications for treatment, the primary healthcare team may choose to initiate counselling, treatment (including for suspected RHD) and/or additional referrals before completion of the full diagnostic echocardiogram.^51^

Any new case of RHD will be notified to the relevant local or jurisdictional RHD register, based on national guidelines in Australia and Timor-Leste.

Data audits will be conducted at least monthly, and if abnormal or uninterpretable SPLASH images have not been appropriately actioned, a reminder will be sent to the relevant healthcare service as a safety net in the context of this study. Referrals or treatment that occur as a result of these reminders will be evaluated separately to those that are generated as a result of the primary healthcare service response to the initial report.

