### Participation and recruitment

Eligible participants are children and young people aged 5–20 years residing in participating communities, and pregnant women at high risk for RHD. Pregnant women are considered to be at high risk if they are Aboriginal or Torres Strait Islander, or if they live in a remote community in northern Australia, or if they have immigrated to Australia from a high-prevalence country with all-age RHD prevalence >1 per 1000 people, or if they live in Timor-Leste. Women, children and young people with known history of ARF, RHD or other existing cardiac disease will not be excluded.

Pathways for recruiting eligible participants will be co-designed with each local community and participating primary healthcare service. We anticipate that this will primarily involve scanning opportunistically in the primary healthcare setting, with occasional organised screening days at local schools or community centres. In some settings, scanning may occasionally occur in the neighbourhoods as guided by trained local staff.

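### The baseline is calculated before recruitment and the end value at completion, with no rule for prescriptions that predate baseline but enter the records in between, so more complete records can count as programme gain

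*Protocol article*

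**What the plan says.** The Evaluation of clinical effectiveness section defines the primary outcome as the change in the proportion prescribed prophylaxis "by the end of the study compared with a baseline timepoint prior to the date of echocardiographic active case finding". The Discussion confirms that no randomised design is used, so this baseline is the only comparator.

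The Quantitative data analysis section fixes when the two proportions are worked out: they "will be calculated prior to recruitment and screening participants, and at completion of the study". One statement covers the source for both: "Numerator data will be obtained from clinic and RHD register data". For the population, "the denominator will be based on census population data or health information system population data".

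Between the two calculations the programme works on the same records:

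- Under Participation and recruitment, people with a "known history of ARF, RHD or other existing cardiac disease will not be excluded".
- Under Clinical effectiveness data collection, "Demographic and clinical data will be obtained from primary healthcare and RHD register data systems by research staff, who will enter data into REDCap". The items listed include "history of known ARF/RHD, clinical management decisions including referrals for formal echocardiography and commencement of secondary prophylaxis".
- Under Embedding task-sharing of SPLASH echocardiography into healthcare delivery, the cardiologist's report is made available to the clinic.

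The Evaluation of clinical effectiveness section also counts, per community, people who start and people who stop prophylaxis during the study, as secondary outcomes. No section says how to treat a prescription that began before baseline but was found afterwards.

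**The concern.** In an uncontrolled comparison, any difference in how completely the two timepoints are measured goes straight into the effect estimate. Naming the same two sources does not make them equally complete at two dates, particularly when the programme leads staff to look at those records in between.

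Take someone who was already prescribed prophylaxis before the study but was missing from the local clinic list and the register when the baseline was calculated. If that person is scanned, or their records are extracted, the prescription may reach the local record and be counted at completion. Nobody has been newly treated, yet the proportion rises.

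At stake is the primary effectiveness claim. The protocol reads a rise in this proportion as better access to guideline-based care. Better record-keeping is a different result and should not be reported as that one.

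**Working it through.** **Inputs.** From the Sample size calculation section: baseline 4.4%, end 6.8%, difference 2.4 points, two-sided 5% significance, 80% power, stated size 1,421, planned enrolment above 1,500. Capture at baseline (*s*) and at completion (*e*) is not given anywhere and is an assumption throughout.

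**1. The plan's own figure.** Unpooled formula per timepoint: (1.960 + 0.842)² × [0.044 × 0.956 + 0.068 × 0.932] / 0.024² = 7.849 × 0.10544 / 0.000576 = 1,437. The pooled version gives 1,440 and the arcsine version 1,425. All lie within 3% of 1,421, so the stated size reproduces. The present point does not affect it.

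**2. The planned effect in people.** 1,500 × 4.4% = 66; 1,500 × 6.8% = 102; gain 36. The 1,500 is a convenient scale, since the actual denominator is the census or health-system population. Results in percentage points do not depend on it.

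**3. The artefact.** If the true proportion stays at *p*, the spurious change is *p* × (*e* − *s*). Equal capture, at any level, gives zero. With *p* = 4.4% and *e* = 100%:

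| Baseline capture *s* | Observed baseline | Spurious rise (points) | People per 1,500 | Share of 2.4 points | Chance of a significant rise |
|---|---|---|---|---|---|
| 98% | 4.31% | 0.09 | 1.3 | 4% | 3.3% |
| 95% | 4.18% | 0.22 | 3.3 | 9% | 4.8% |
| 90% | 3.96% | 0.44 | 6.6 | 18% | 8.7% |
| 80% | 3.52% | 0.88 | 13.2 | 37% | 23.4% |

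Example for 90%: 4.4% × 0.10 = 0.44 points; 0.44 / 2.4 = 18%; 0.0044 × 1,500 = 6.6 people.

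The last column is the power of a two-sided 5% test of two independent proportions with 1,500 per timepoint and no true change; the nominal upper-tail rate is 2.5%. It is a rough guide, because it ignores clustering and the overlap of people between timepoints.

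**4. If only some missed people are found.** With a share *c* of them found, the rise is *p* × (1 − *s*) × *c*. At *c* = 50% the 0.44 and 0.88 points become 0.22 and 0.44. This matters because the described extraction concerns participants, while the numerator covers the whole target population.

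**5. If the programme works as planned.** With a true rise from 4.4% to 6.8% and 90% baseline capture, the observed rise is 6.8 − 3.96 = 2.84 points instead of 2.4, an overstatement of 18%.

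**The case against.** The strongest reply is that one source rule governs both timepoints. A prescription already in a clinic or register record is available at baseline, and no section describes a thinner search then. This stands as far as it goes: the bias needs records that become more complete during the study, which the protocol neither states nor rules out.

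A reader might infer more: that history-taking, monthly audits and register notification will uncover old prescriptions, and so the end proportion is certain to be inflated. The text does not support that.

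- The data collection section describes extraction from record systems, with no separate participant interview feeding the numerator.
- The sentence beginning "Data audits will be conducted at least monthly" concerns whether abnormal or uninterpretable scans were acted on. It does not describe a search for older prescriptions, and treatment that follows a reminder is evaluated separately.
- Only new cases are notified to the register.
- People with known disease are merely not excluded; the programme does not seek them out.
- The bias need not run one way. Closer review may also remove people who moved, finished treatment or were entered twice, which lowers the end proportion.

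The counts of starts and stops offer a partial check: a rise larger than net starts would point to late-found prescriptions. This works only if a start is classified by prescription date, which is not stated, and it leaves the primary estimate uncorrected.

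Finally, re-dating rules might sit in an analysis plan that is not shown. But this article itself fixes when the baseline is calculated, and that choice creates the exposure.

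**Conclusion.** The point holds as a risk built into the stated timing; it is not a demonstrated bias. Calculating the sole comparator before recruitment, with no rule to re-date later discoveries, allows improved records to be read as increased prescribing.

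The size is unknown. If 5% of existing prescriptions were missed at baseline, the artefact is small. At 10% to 20% missed and all found, it is about a fifth to over a third of the planned effect. These figures assume full capture at completion, no stale entries removed and recovery of every missed person; relaxing any of these shrinks them. The general acknowledgement under Limitations and strengths that other factors may influence the outcome does not name this one, and adjusting for clustering does not remove it. A change is worthwhile because a better method is available at little cost.

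**What to change.** In the Quantitative data analysis section:

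1. Derive both primary numerators at completion, by the same method and from the same clinic and register sources, using prescription start and stop dates to set each person's status on the site's baseline date and on the end date.
2. Count a person at a given date only if they belonged to the target population on that date, by age or pregnancy and by residence. Without this condition, a child who was under 5 at baseline, or someone who moved in later, could enter the baseline numerator without being in its denominator.
3. Apply late-found additions and late-found removals alike.
4. Keep the proportion calculated before recruitment as a sensitivity analysis, and report how many people were reclassified in each direction.

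The cost is a second extraction of dated records. The sources are already in the plan, Table 3 already lists initial prescription as a variable, and stops are already to be counted. The estimated increase may turn out smaller.

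### The primary p-value is stated without the clustering adjustment given to its own confidence interval, so its error rate is not controlled at 5% and the two can disagree

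*Protocol article*

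**What the plan says.** Under Quantitative data analysis, consecutive sentences treat the same change in two ways. The estimate: "The absolute change in proportion of the target population prescribed prophylaxis will be calculated with adjustment for clustering by community and described with 95% CIs". The test: "Proportions from commencement and completion of the study will be compared using a two-tailed comparison of proportions test". The decision rule follows: "A p value <0.05 will be considered significant". Table 3 lists the same comparison for the primary outcome and names no adjustment.

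The Sample size calculation section plans for an "absolute increase of 2.4% of the target population prescribed secondary prophylaxis, from a baseline prevalence of 4.4% to 6.8" per cent, "with 95% two-sided significance and 80% power, the sample size required is 1421". Enrolment is to be spread "across approximately 10 sites (~150 participants per site". No design effect or within-person correlation is mentioned.

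The denominator at each time point is a census or health-system count of the community's target population, not the enrolled sample. That population is children and young people aged 5–20 and pregnant women. People already known to have ARF or RHD are not excluded.

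**The concern.** A comparison of two proportions, taken at its name, assumes two independent simple random samples. Two features of this design break that assumption, in opposite directions.

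- **Communities differ in their change.** The programme is tailored by site, and the evaluation expects success to differ across sites. Spread in the true changes adds variance that the test does not see, so it rejects too often.
- **The same people are counted twice.** A resident prescribed prophylaxis at the start is likely still to be prescribed it at the end. This positive correlation reduces the variance of the change, so the test rejects too seldom.

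The interval is to allow for clustering and the test, as written, is not, so the two rest on different standard errors. At stake is the only significance criterion that the article declares for its primary outcome.

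**Working it through.** **1. Which test does the sample size imply?** Inputs from the Sample size calculation section: 4.4%, 6.8%, two-sided 5%, 80% power. The unpooled two-sample formula gives

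n = (1.96 + 0.842)² × (0.044×0.956 + 0.068×0.932) / 0.024² = 7.849 × 0.10544 / 0.000576 ≈ 1437 per time point.

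The pooled-variance version gives 1440. The stated 1421 is within 1.3% of these; power at 1421 is 79.5%. Other formulas do not fit: continuity-corrected 1522, one-sided 1134, one-sample 655, paired (McNemar) 325 to 1143 pairs for 0% to 3% stopping. So 1421 matches an independent two-sample comparison with no design effect.

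**2. How much overlap is plausible?** Ages 5–20 span 16 years. Ageing out removes about 1.5/16 = 9% over 18 months, or (34/12)/16 = 18% over the 34 months from August 2022 to June 2025. About 82–91% of that group stays eligible, ignoring migration. Pregnant women mostly turn over. The mix of the two groups is not given.

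**3. Type I error with both dependencies.** Let VR be the true variance of the overall change divided by the variance the test assumes. With proportion p = 5%, m people per site, and SD the spread of true community changes around a mean of zero:

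- No overlap: VR = 1 + m·SD² / [2p(1−p)], where 2p(1−p) = 0.095.
- Full overlap, with an assumed 4.4% of people changing status: VR = 0.044/0.095 + m·SD²/0.095.
- True size of the nominal 5% test = 2[1 − Φ(1.96/√VR)].

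| m per site | Overlap | SD 0 | SD 1.5 points | SD 2.0 points |
|---|---|---|---|---|
| 150 | none | 5% | 9% (VR 1.36) | 12% (VR 1.63) |
| 150 | full | 0.4% (VR 0.46) | 3% (VR 0.82) | 6% (VR 1.09) |
| 600 | none | 5% | 21% (VR 2.42) | 30% (VR 3.53) |
| 600 | full | 0.4% (VR 0.46) | 15% (VR 1.88) | 26% (VR 2.99) |

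Simulation agrees with these values to within about a percentage point. A paired t-test on the 10 community differences stays at about 5% in every cell. SD, overlap, the 4.4% and the 600 are assumptions. The 150 is the enrolment target, and the actual denominators are community counts that may be larger.

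**4. Can p-value and interval disagree?** Take 1500 people at each time point and an observed rise from 4.4% to 6.8%.

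- Test: pooled SE = √(2×0.056×0.944/1500) = 0.840 points; z = 2.4/0.840 = 2.86; p = 0.004.
- Interval: unadjusted SE = √(0.10544/1500) = 0.838 points. The interval includes zero once VR exceeds (2.4/(1.96×0.838))² = 2.13, or (2.4/(2.262×0.838))² = 1.60 with t on 9 df. At VR 2.5 (normal reference) it runs from −0.2 to +5.0 points.
- With 150 per site and no overlap, these thresholds need SD = √((VR−1)×0.10544/150), which is 2.8 points for VR 2.13 and 2.1 points for VR 1.60. Smaller observed changes need less: with a normal reference the two disagree whenever z lies between 1.96 and 1.96√VR, for example 1.96 to 2.50 at VR 1.63.

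Reverse case: the same 1500 people measured twice with no site variation, 4.4% to 5.4%, with 0.5% stopping and 1.5% starting. The two-sample test has SE 0.788 points and z = 1.27, so p = 0.20. The paired SE is √((0.020 − 0.010²)/1500) = 0.364 points, giving a 95% interval of +0.3 to +1.7 points.

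**The case against.** The strongest reply is that the article never calls its test ordinary, independent or two-sample. The test sentence follows directly on the cluster-adjusted change, a comparison of proportions can itself be cluster-adjusted, and a full analysis plan may say so. This limits certainty about what will be run. It does not clear the text, which attaches the adjustment to the interval only, repeats the test without it in Table 3, and plans its sample size on the independent formula.

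A reader might infer that the test inflates false positives. The documents do not support a direction. With full overlap and 150 per site, the two errors largely cancel (3–6% at SD 1.5–2.0 points). The 9–12% figures need separate people at each time point, which sits badly with a population that largely persists.

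A reader might also infer a severe loss of power from ignoring pairing. With 1500 fixed people, 1.0% stopping and 3.4% starting, the correct SE is 0.54 points against 0.84. At the planned 2.4 points, power is about Φ((2.4 − 1.96×0.84)/0.54) = 92% unpaired against 99% paired. A large gap appears only at effects well below the planned one. The protocol does not define a fixed cohort of 1500 in any case, because its denominators are population counts.

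Finally, the article already promises a cluster-adjusted interval and results by community, and it acknowledges influences other than the intervention. That softens the consequence of a wrong p-value but leaves the stated test inconsistent with the interval.

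**Conclusion.** The point holds as an inconsistency in the stated primary analysis. One change is given two variance treatments, and the one that produces the p-value ignores both clustering and repeated counting of people. Its true error rate matches 5% only if the two effects happen to cancel.

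Under the assumed ranges, the size is about 0.4% to 12% at 150 people per site and 0.4% to 30% at 600. The documents give neither the SD of community changes, nor the overlap, nor community size, so neither direction nor amount can be settled from them. The conclusion rests on reading the test by its name, on the absence of any adjustment in both places where it is described, and on the match of 1421 to the independent formula. Extensive overlap is an inference for ages 5–20 and does not extend to pregnant women.

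**What to change.** Use one analysis for both the 95% interval and the p-value: the before/after difference in each community, weighted by denominator, with a t reference on communities minus 1 df (minus 2 if stratified by country). Replace the separate comparison of proportions with this under Quantitative data analysis and in Table 3. It works with census or health-system denominators. A person-level repeated-measures model, with community-robust variance and a small-sample correction, is an option only where individual records can be linked across the two time points.

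The change needs no new data. Its cost is precision: the critical value with 10 communities is about 2.26 instead of 1.96, so the interval may widen. The Sample size calculation section should also say that 80% power at 1421 is based on an independent, unclustered comparison, because power under the replacement analysis depends on the spread of community changes, which the article does not give.
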